### **10.2. Definition of Serious Adverse Events**

A serious adverse event is any untoward medical occurrence that

- results in death
- is life-threatening
- requires inpatient hospitalisation or prolongation of existing hospitalisation
- results in persistent or significant disability/incapacity
- consists of a congenital anomaly or birth defect.

Other 'important medical events' may also be considered a serious adverse event when, based upon appropriate medical judgement, the event may jeopardise the participant and may require medical or surgical intervention to prevent one of the outcomes listed above.

NOTE: The term "life-threatening" in the definition of "serious" refers to an event in which the participant was at risk of death at the time of the event; it does not refer to an event which hypothetically might have caused death if it were more severe.

### **10.3. Reporting Procedures for Serious Adverse Events**

A serious adverse event (SAE) occurring to a participant will be reported to the REC that gave a favourable opinion of the study where in the opinion of the Chief Investigator the event was 'related' (resulted from administration of any of the research procedures) and 'unexpected' in relation to those procedures. Reports of related and unexpected SAEs will be submitted within 15 working days of the Chief Investigator becoming aware of the event, using the HRA report of serious adverse event form (see HRA website).

### **10.4. Reporting Procedures for Device Related Adverse Events**

All patients in this study will have MRI conditional implantable cardiac devices as defined by the inclusion criteria. All patients' cardiac implantable devices (ICD or CRT-D devices) will be set in an MRI safe mode for the duration of the scan, in accordance with the individual manufacturer's conditions and following local clinical protocols. Furthermore, as part of the individual planning of each participant's radiotherapy, the radiation dose to their device will be considered and must be below their tolerance constraints as defined by the UK Consensus (63) and American Association of Physicists in Medicine (AAPM) guidelines (64).

However, it is still theoretically possible that a device complication could occur despite adherence to these protocols. If a device related complication occurs, we will notify the device manufacturer within 1

working day for further investigation. If the device related complications affect clinical safety of the participant, immediate appropriate clinical action will be taken, which could include admission to the cardiology ward for further assessment and treatment. If such complications amount to an SAE (as defined in 10.2) and investigators consider such complications 'related' (resulted from administration of any of the research procedures) and 'unexpected' in relation to study procedures these will also be reported to REC as outlined in section 10.3.

#### **10.5. Follow-up of Serious Adverse Events**

In the event of an SAE, participants will remain under study follow up for the duration of the study to monitor the progress of the SAE. If deemed clinically appropriate by the investigators, and with the consent of the patient, onward clinical referral to the appropriate clinical specialty will be arranged for further investigation and treatment of symptoms. This study will monitor and report on SAE which occur within the pre-specified monitoring window period as discussed in section 10.0. Following completion of the study, all patients will return to routine clinical follow up as part of their routine clinical care. This will include follow up under the device clinic and, where applicable, by the heart failure and arrhythmia service.

### **11. STATISTICS AND ANALYSIS**

#### **11.1. Statistical Analysis Plan (SAP)**

The plan for the statistical analysis of the study are outlined below. There is not a separate SAP document in use for the trial.

#### **11.2. Description of the Statistical Methods**

To measure our primary safety endpoint, we will measure the frequency of adverse events in the 6 months post radiotherapy. Our trial is powered to detect adverse event rates of 34% (see below)

For secondary outcome measures such as changes in circulating biomarker levels (NPY) and changes in number of device therapies following radiotherapy we will use non-parametric tests such as a Wilcoxon signed rank test to determine if changes are statistically significant.

To assess correlation between changes in biomarker levels and number of device therapies we will use a correlation matrix using non-parametric correlation tests such as Spearman rank-order correlation.

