| Secondary objectives                                                                                                                          |                                                                                                                                                                                                                               |                                                                                                          |
| Assess the feasibility of hypofractionated radiotherapy to modify the stellate ganglia to achieve anatomical and functional sympathetic denervation. | Physical modification of the stellate ganglia as assessed on MRI imaging                                                                                                                                                      | MRI scan at the final study visit 6 months post radiotherapy                                             |
|                                                                                                                                                      | Haemodynamic evidence of stellate ganglia modification determined by clinical and device-based heart rate dynamics and variability                                                                                            | Monitoring visits up to 6 months post radiotherapy                                                       |
|                                                                                                                                                      | Changes in circulating biomarker levels                                                                                                                                                                                       | Monitoring visits up to 6 months post radiotherapy                                                       |
|                                                                                                                                                      | The number of ventricular arrhythmias requiring device therapy                                                                                                                                                                | Monitoring visits up to 6 months post radiotherapy                                                       |

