|                                                                                                                                                      | Patient reported outcomes about quality of life and symptoms based on KCCQ questionnaire                                                                                                                                      | Monitoring visits up to 6 months post radiotherapy                                                       |

|                                                                                                                                                                      |                                                                                                                                                                                          |                                                                             |
|----------------------------------------------------------------------------------------------------------------------------------------------------------------------|------------------------------------------------------------------------------------------------------------------------------------------------------------------------------------------|-----------------------------------------------------------------------------|
| Correlate the change in circulating biomarker levels with the efficacy of hypofractionated radiotherapy to modify the stellate ganglia in terms of arrhythmic burden | Changes in serum biomarker levels prior to compared to following intervention. Reduction in the number of ICD shocks/ATP in the 6 months before compared to the 6 months after treatment | During initial visit and monitoring visits up to 6 months post radiotherapy |
|----------------------------------------------------------------------------------------------------------------------------------------------------------------------|------------------------------------------------------------------------------------------------------------------------------------------------------------------------------------------|-----------------------------------------------------------------------------|

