### 8.2. Inclusion Criteria

#### General Inclusion Criteria

- Participant is willing and able to give informed consent for participation in the study.
- Male or Female, aged at least 18 years old.
- Known diagnosis of structural heart disease defined as any patient with impaired left ventricular ejection fraction (less than 55%) due to any cause including ischaemic cardiomyopathy, dilated cardiomyopathy, hypertrophic cardiomyopathy or Arrhythmogenic cardiomyopathy.
- CMR compatible ICD device implanted a minimum of 6 months ago, under follow-up at Oxford University Hospitals NHS Foundation Trust.
- Experienced more than one appropriate ICD therapy (shocks or ATP) for ventricular arrhythmia in the last 6 months
- Established on optimal guideline based medical therapy for heart failure and arrhythmia

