### **9.8. Early Discontinuation/Withdrawal of Participants**

During the course of the study a participant may choose to withdraw early from the study treatment at any time. This may happen for several reasons, including but not limited to:

- The occurrence of what the participant perceives as an intolerable AE.
- Inability to comply with study procedures
- Participant decision

Participants may choose to stop treatment and/or study assessments but may remain on study follow-up.

Participants may also withdraw their consent, meaning that they wish to withdraw from the study completely.

According to the design of the study, participants may have the following three options for withdrawal;

- 1) Participants may withdraw from active follow-up and further communication but allow the study team to continue to access their medical records and any relevant hospital data that is recorded as part of routine standard of care; i.e., Remote monitoring of their ICD.
- 2) Participants can withdraw from the study but permit data and samples obtained up until the point of withdrawal to be retained for use in the study analysis. No further data or samples would be collected after withdrawal.
- 3) Participants can withdraw completely from the study and withdraw the data and samples collected up until the point of withdrawal. The data and samples already collected would not be used in the final study analysis. A limitation to this withdrawal would be any data that has already been used as part of interim analysis, including by the independent safety committee.

In addition, the Investigator may discontinue a participant from the study treatment at any time if the Investigator considers it necessary for any reason including, but not limited to:

- Pregnancy
- Ineligibility (either arising during the study or retrospectively having been overlooked at screening)
- Significant protocol deviation
- Significant non-compliance with treatment regimen or study requirements
- Clinical decision

The type of withdrawal and reason for withdrawal will be recorded in the CRF.

Withdrawn participants will be replaced

Patients who have withdrawn from the study who also opt out of further study follow up will continue to be followed indefinitely up as part of their routine clinical care. This will include follow up under the device clinic, and where applicable by the heart failure and arrhythmia service.

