## **10. SAFETY REPORTING**

This study is primarily a safety study and is specifically powered to detect SAEs (see section 11.3). The safety reporting window will be from the first fraction of radiotherapy until completion of the 6 months study follow up. A 6 months SAE reporting window is felt to be sufficient as adverse events related to cardiac sympathetic denervation should be apparent during treatment or within days, weeks or months of completion of radiotherapy if we consider trigeminal neuralgia as a parallel (78). Indeed, over the course of 6 months we will monitor any adverse events and side-effects and the expectation is that side effects will improve rather than worsen over this time period, as is observed following surgical removal of the stellate ganglia(20)

With respect to adverse events following radiotherapy, we expect to detect any dose limiting toxicity within 6 weeks of completion of radiotherapy, which is an accepted monitoring period for dose escalation trials involving radiotherapy (79). In terms of stochastic adverse effects, in the long term, ionising radiation can also cause cancer which manifests itself after many years or decades and is an accepted side-effect of the treatment. It is not likely that we would detect such adverse events even if our reporting window was extended beyond 6 months. Indeed, our study population of patients with severe heart failure and recurrent ventricular arrhythmias has a particularly poor prognosis, even despite all current available medical therapies, with mortality rates observed in excess of 50% at 5 years(67). As such late stochastic events might never become apparent.

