#### **11.4. Analysis populations**

All participants who completed their course of radiotherapy bilaterally to the stellate ganglia (an adverse event analysis).

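### ICD therapies are compared as raw counts over nominal 6-month windows, so an 'after' window cut short by death or option 2 withdrawal, if counted as observed, leans the result towards improvement

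*Protocol*

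**What the plan says.** Section 6 (repeated in the synopsis) defines the measure as "Reduction in the number of ICD shocks/ATP in the 6 months before compared to the 6 months after treatment", alongside a second count, "The number of ventricular arrhythmias requiring device therapy". Section 11.2 says that for "changes in number of device therapies following radiotherapy we will use non-parametric tests such as a Wilcoxon signed rank test" will be applied, and that the change in therapies will be correlated with the biomarker change by a rank correlation such as Spearman's. Neither section mentions a rate, a time denominator or a rule for death. Section 11.1 closes off any later document: "There is not a separate SAP document in use for the trial".

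Eligibility (section 8.2) requires a "CMR compatible ICD device implanted a minimum of 6 months ago" and more than one appropriate therapy in the last 6 months. Section 9.8 offers three forms of withdrawal. Option 1 keeps access to records, with remote ICD monitoring as its example. Option 2 stops collection but lets participants "permit data and samples obtained up until the point of withdrawal to be retained for use in the study analysis". Option 3 removes the data. Withdrawn participants are replaced; death is not mentioned there. The only analysis set, in section 11.4, is "All participants who completed their course of radiotherapy bilaterally to the stellate ganglia", labelled as an adverse event analysis. Section 10 describes the population as having "mortality rates observed in excess of 50% at 5 years".

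**The concern.** A count depends on how long the device was watched. Here the exposure can be unequal in one direction only: the 'before' period is always complete, and the 'after' period ends early if the participant dies or stops data collection under option 2. Set against a full 'before' count, a short 'after' count looks like fewer therapies whether or not radiotherapy did anything.

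The outcome addresses one of the protocol's stated research questions, whether radiotherapy reduces abnormal rhythms and whether that tracks the blood markers. With no control group, nothing in the data would expose the artefact, and the same distorted change would also feed the biomarker correlation. The most awkward case is a participant who dies of the arrhythmia under treatment and contributes a favourable difference.

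**Working it through.** The protocol gives no sample size, power or expected rate for device therapies, so there is no stated figure to reproduce. The 13 comes from the serious adverse event endpoint and is taken as given.

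**Inputs from the protocol.** n = 13; ICD in place at least 6 months and more than one therapy in 6 months (8.2); more than 50% mortality at 5 years (10).

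**Assumptions.** Constant hazard of death; no treatment effect; Poisson counts; the therapy rates and cut-off times given below; a short window counted as observed.

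**Step 1. One participant followed for 2 of 6 months.** With a constant rate equal to the 'before' count b, the later count is Poisson with mean b × 2/6. The chance of a lower count is P(X ≤ b − 1).

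| Therapies before | Expected in 2 months | Chance of a lower count, 2 months | Chance of a lower count, full 6 months |
|---|---|---|---|
| 2 | 0.67 | 86% | 41% |
| 4 | 1.33 | 95% | 43% |
| 6 | 2.00 | 98% | 45% |

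When rates also vary between participants (Step 4), 74 to 86% of those followed for 2 months show a lower count.

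**Step 2. How often the window is cut by death.** 6-month risk = 1 − 0.5^(0.5/5) = 0.067. Expected deaths = 13 × 0.067 = 0.87. Chance of none = 0.5^1.3 = 0.406, so of at least one 0.594. Chance of exactly one = 0.87 × 0.5^1.2 = 0.379, so of two or more 1 − 0.406 − 0.379 = 0.215. Three or more: about 5%.

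The protocol gives no 6-month figure and no rate of option 2 withdrawal. If the combined risk is anywhere from 5% to 20%, the expected number is 0.65 to 2.6 and the chance of at least one is 49 to 95%.

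**Step 3. Shift in the total.** If k of 13 are observed for 2 of 6 months, the expected share of 'after' therapies missed is (k/13) × (4/6): 5.1% for k = 1, 10.3% for k = 2.

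**Step 4. Effect on the Wilcoxon test.** Simulation with no effect, n = 13, one-sided 2.5% towards improvement, participant rates from a gamma distribution (shape 1.5, mean 4 or 8 per 6 months), k participants cut at 2 months, 2,000 runs per cell. The simulation error near 2.5% is about √(0.025 × 0.975/2000) = 0.35 percentage points.

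| Participants cut short | Raw count, mean 4 | Raw count, mean 8 |
|---|---|---|
| 0 | 2.8% | 2.6% |
| 1 | 2.5% | 4.7% |
| 2 | 6.0% | 5.7% |
| 3 | 7.7% | 9.7% |
| 4 | 12.3% | 15.7% |

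Dividing each count by observed time gives 2.0 to 2.8% in nine of the ten cells and 3.8% in the other (mean 8, four cut short).

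A second set-up (gamma shape 1.5, mean 8, plus 2 per 6 months; cut at a uniformly random time) gives 2.5% with none, 3.4% with one and 4.7% with two.

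**The case against.** **The protocol never says a partial window is counted as observed.** The outcome is defined on 6 months after treatment, so a participant with 2 months of data could equally be dropped as lacking it. Section 11.4 does not settle this, because its label ties that set to the adverse event analysis and no set is named for device therapies. This stands: the bias is conditional. The silence is still a fault, because option 2 retains partial data for analysis and no other document will decide.

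**A reader might infer that such participants are always scored as improved.** That does not follow. A short window cannot raise a count, but a participant dying of arrhythmia may accrue many therapies first, and section 5 itself links recurrent device therapy to higher mortality. Step 1 shows a strong tendency under independence, not a certainty.

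**A reader might take the 20% drop-out allowance to mean that about three of the 13 are cut short.** The protocol does not support this. The allowance concerns screening 16 to obtain 13 (16 × 0.8 = 12.8). Withdrawals are replaced, option 1 keeps the ICD data and option 3 removes the participant's data. What remains is death and option 2 withdrawal after treatment, so the rows for three and four participants are adverse scenarios, not the expectation.

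**The outcome is secondary and unpowered, and a death would be reviewed as a serious adverse event.** That is true and limits the stakes. It does not repair the efficacy comparison or the correlation.

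**A rate alone does not make death a bad outcome.** This also stands: a fatal arrhythmia with few earlier therapies would still give a low rate. A rule for death is needed as well.

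**Conclusion.** The point holds in a limited form. The plan fixes a count with no allowance for observed time and no rule for death. Only the 'after' window can be short, so a short window counted as observed pushes the paired change towards improvement. With about one death expected in 13 (59% chance of at least one), one-sided false improvement moves from about 2.5% to between 2.5% and 4.7%. With two shortened windows it is about 5 to 6%. Larger distortions need three or more, which deaths alone would produce about 5% of the time.

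These figures rest on a constant hazard at exactly 50% 5-year mortality, on therapy rates and cut-off times that the protocol does not give, and on early ending being unrelated to arrhythmia burden. The finding concerns the device-therapy outcome and its correlation with biomarkers; the primary safety endpoint is not affected. It is worth correcting because the remedy is cheap and, without controls, the artefact could not be seen in the results.

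**What to change.** In sections 6 and 11.2:

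- Define the measure as appropriate ICD therapies per month of observed ICD monitoring, before and after radiotherapy, and use it in both the Wilcoxon test and the biomarker correlation. End the 'after' time at death or loss of device data, and at 6 months otherwise.
- For option 1 withdrawals, use the remote-monitoring data for the full 6 months, as section 9.8 already allows.
- List each participant's observed months before and after, and any death, beside the rate.
- Add a sensitivity analysis in which death within 6 months is ranked as the worst outcome.

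The cost is a few sentences. The study team already plans to take therapies from the pacing clinic's remote-monitoring records, and the same records should supply the monitoring dates. The small downside is that a rate from very short follow-up is noisy; listing the months makes that visible.

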#### **11.3. Sample Size Determination**

Considering that all patients will have failed pharmacological treatments to prevent VT, the population is expected to be at particularly high risk and SAE rates  $\leq 34\%$  (as reported for surgical CSD), and efficacy rates of 50% would be clinically acceptable. To be 80% powered to demonstrate a SAE rate not

exceeding 34% (range 9-34%) on a one sided, one sample test for proportions (alpha 0.05) would require 13 patients. Considering that all patients will have failed pharmacological treatments to prevent dangerous heart rhythms, the population is expected to be at particularly high risk of further dangerous heart rhythms. Efficacy rates of 50% would be clinically acceptable. We anticipate screening at least 16 patients to allow for a 20% drop out rate, **which has been costed in our BHF grant.**

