Unfortunately, this procedure also carries a high complication rate. In a systematic review, including 173 patients, complications occurred in 34% of patients.(19).Surgical complications include pneumothorax, haemothorax and wound complications, with reported frequency up to 15% (19, 39, 40). Even more commonly, in up to 30% of patients, off-site neurological effects such as upper limb neuropathic pain, altered sweating, Horner's syndrome and transient hypotension occur. These are however generally mild and transient(19, 41), and importantly even when they do persist don't affect patients' quality of life (42, 43). Interestingly it seems that many of the off-site neurological complications result from the physical manipulation and damage of nerves during surgery. Furthermore, recent evidence suggests that the risk of Horner's syndrome and hyperalgesia may be mitigated by sparing the cranial portion of the stellate ganglion, and the T3-T4 paravertebral ganglia whilst still achieving sufficient CSD(30).

We thus hypothesise that a non-invasive technique, targeting the lower half of the stellate ganglia bilaterally, aiming for modification rather than complete destruction would provide a more favourable complication profile whilst maintaining anti-arrhythmic efficacy. Indeed, recently Nonoguchi et al. described transiently achieving successful CSD using phototherapy of the stellate ganglion without complications(44).

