### **Cardiac sympathetic denervation**

The aim of delivering radiotherapy to the stellate ganglion in this study is to achieve functional sympathetic denervation of the heart. Reports about the type and frequency of complications arising from cardiac sympathetic denervation come from case series of surgical removal of the stellate ganglion. A large number of complications associated with this are surgical complications such as pneumothorax, pleural effusion and infection, which do not apply to our study, and indeed is part of the motivation for this study to achieve CSD in a non-invasive manner.

The primary non-surgical complications associated with CSD are off site neurological effects and hypotension. A recent systematic review including 173 patients who had surgical CSD estimated the risk of hypotension as 9%, and off-site neurological effects as follows: Horner's syndrome 3%, and upper limb and face hyperalgesia 4% and hypohidrosis 3%(19). No procedural deaths were reported. The risk of Horner's syndrome can be mitigated by sparing the cranial portion of the stellate ganglion and sparing the T3-T4 paravertebral ganglia may reduce off site neurological complications while still achieving sufficient CSD(30). Overall experience from surgical removal of the stellate ganglia suggests that off-site neurological side effects generally mild and transient(19, 41), and importantly even when they do persist don't significantly affect patients' quality of life (42, 43).

Our study is designed to minimise the risk of complications. We will only target the lower half of the stellate ganglia and T1-2 paravertebral chain. Furthermore, by achieving CSD in a staged and stepwise manner over 3 fractions of radiotherapy we aim to detect any complications early before permanent CSD is achieved, thus mitigating the severity of these complications. Indeed, one of the co-primary outcomes of this study is any treatment related adverse effects.

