#### **11.7. The Level of Statistical Significance**

We are 80% powered to demonstrate a SAE rate not exceeding 34% (range 9-34%) on a one sided, one sample test for proportions (alpha 0.05).

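### The 34% SAE limit is surgery's overall complication rate, so meeting it would not show that radiotherapy is as safe as surgery

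*Protocol*

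**What the plan says.** Section 11.3 (Sample Size Determination) calls an SAE rate of up to 34% clinically acceptable and gives its source in parentheses: "as reported for surgical CSD), and efficacy rates of 50% would be clinically acceptable". It then sizes the trial to show a rate not "exceeding 34% (range 9-34%) on a one sided, one sample test for proportions (alpha 0.05) would require 13 patients". Section 11.7 repeats the limit and the test.

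The only origin of 34% in the protocol is section 5, under Cardiac sympathetic denervation: "In a systematic review, including 173 patients, complications occurred in 34% of patients". No grade or seriousness criterion is attached. The same paragraph puts operative complications at up to 15% and off-site neurological effects at up to 30%, and says of the latter: "These are however generally mild and transient".

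Section 9.4.1 describes a large share of the surgical harms as "surgical complications such as pneumothorax, pleural effusion and infection, which do not apply to our study". For the non-surgical harms, it says the same systematic review "estimated the risk of hypotension as 9%, and off-site neurological effects as follows": Horner's syndrome 3%, hyperalgesia 4%, hypohidrosis 3%.

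The first primary outcome (Synopsis, section 6) counts treatment-related grade 3 toxicity leading to hospitalisation, or grade 4 to 5 toxicity, within 6 months. Section 7, the Figure 2 legend and section 11.6 also require the event to be unexpected. The second primary outcome is treatment-related side effects from questionnaires and examination.

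**The concern.** The limit and the endpoint measure different things. The 34% counts surgical patients with a complication, including operative injuries and mild neurological effects. The trial's numerator counts only severe, treatment-related events. The protocol reports no surgical SAE rate, so the attribution in section 11.3 has no support in the document.

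This matters because a comparison with surgery is intended. One research question in section 5 asks whether the safety profile is favourable against alternatives that include surgical removal. Section 16.4.1 hypothesises a lower complication rate than surgery. A result below 34% on the severe endpoint could be read as support for either statement, and it would support neither. The error leans towards reassurance about a new procedure.

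**Working it through.** **1. The plan's own figure.** Inputs from sections 11.3 and 11.7: rates 9% and 34%, one-sided alpha 0.05, power 80%. The text does not label the 9%; it is taken here as the second rate in the calculation.

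n = [1.645·√(p0(1−p0)) + 0.842·√(p1(1−p1))]² / (p0−p1)²

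- Null 9%, alternative 34%: (0.471 + 0.399)²/0.0625 = 12.09, so 13. This matches the protocol.
- Null 34%, true rate 9%, as sections 11.3 and 11.7 read: (0.779 + 0.241)²/0.0625 = 16.65, so 17. An exact binomial calculation also gives 17.

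The stated 13 therefore comes out only when the test runs the other way. That agrees with section 11.2, which speaks of detecting a 34% rate. This is a separate inconsistency. The steps below follow sections 11.3 and 11.7, with 34% as the null.

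**2. What passing requires.** The protocol gives no pass threshold, so it is derived here from an exact test with n = 13:

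- P(X ≤ 1 | 0.34) = 0.66¹³ + 13·0.34·0.66¹² = 0.0045 + 0.0302 = 0.035
- P(X ≤ 2 | 0.34) = 0.128

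The test passes with at most 1 SAE in 13. The one-sided 95% upper bound is then 20.6% (0/13) or 31.6% (1/13). That is a statement about severe related events only.

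**3. Benchmark and endpoint side by side.**

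| | Surgical 34% (section 5) | Trial endpoint (Synopsis, sections 6 and 7) |
|---|---|---|
| Severity | no threshold stated | grade 3 with hospitalisation, or grade 4-5 |
| Operative injuries | included (up to 15%) | cannot occur |
| Mild off-site effects | included | not counted |
| Known effects such as hypotension or Horner's syndrome | included | may be excluded where the event must be unexpected, since section 9.4.1 lists them as side effects |

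**4. Illustration.** The share of surgical complications that are severe is not in the documents; 10-30% is an assumption. Suppose radiotherapy had exactly surgery's 34% overall rate. With p = 0.34 × severe share, P(pass) = (1−p)¹³ + 13p(1−p)¹²:

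| Severe share | SAE rate p | P(pass) |
|---|---|---|
| 10% | 3.4% | 0.638 + 0.292 = 0.93 |
| 20% | 6.8% | 0.400 + 0.380 = 0.78 |
| 30% | 10.2% | 0.247 + 0.365 = 0.61 |

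A treatment no safer than surgery overall would thus usually meet the limit in this range.

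**5. The non-surgical part.** The components in section 9.4.1 sum to 9 + 3 + 4 + 3 = 19% if no patient had more than one. This equals 34% less the 15% operative figure in section 5. It is still not a severe rate. Thirteen patients could not demonstrate a rate below 19% in any case: with no events at all, 0.81¹³ = 0.065, above 0.05.

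**The case against.** A sponsor may choose any acceptability ceiling. Section 11.3 also offers a clinical reason: patients whose drug treatment has failed and who are at high risk. This stands. The limit itself is not shown to be wrong; its attribution to surgery is.

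Participant protection does not depend on this test. Sections 7 and 10.1 tie escalation, committee review and pausing to individual SAEs, and the study is an uncontrolled case series. This also stands, and it confines the point to what the trial may conclude.

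The comparison with surgery need not rest on the SAE test, because section 16.4.1 links its hypothesis to the co-primary outcome of treatment-related adverse effects. This is fair, and the fix builds on it. But section 11.3 places the surgical figure on the SAE endpoint, where it does not belong.

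A reader might infer four stronger things that the documents do not support:

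- That passing would say nothing. It would exclude a severe related SAE rate of 34% or more.
- That a treatment worse than surgery would usually pass. Surgery's severe rate is not given, so this cannot be computed. In the illustration the true SAE rate is 3-10%, so concluding that it is below 34% would be correct. The fault lies in reading that result as a comparison with surgery. At true severe rates of 15% and 19%, passing falls to 40% and 26%.
- That the 9% is the review's hypotension rate. The figures coincide, but sections 11.3 and 11.7 do not label it.
- That 34% is clearly the null. Sections 11.3 and 11.7 read so, but section 11.2 and the way 13 is reproduced point the other way.

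**Conclusion.** The point holds as an error of attribution and interpretation. Section 11.3 presents an overall complication rate as an SAE rate and applies it to a much narrower endpoint. Meeting the limit would show a severe related SAE rate below 34%. It would not show that the treatment is as safe as, or safer than, surgery.

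The pass probabilities of 93% to 61% rest on the assumed 10-30% severe share and on an exact test with 34% as the null. The mismatch itself rests on neither. That the 34% spans all grades is inferred from the absence of a threshold and the inclusion of mild effects in section 5; the inference is firm. The 19% assumes no overlap, and it is not an upper limit for non-operative harm, because section 5 cites off-site effects of up to 30%.

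**What to change.** - **Section 11.3:** delete the surgical attribution as the basis for the SAE limit. Either justify 34% as a stand-alone acceptability ceiling with its own rationale, or drop it. Make section 11.7 consistent.
- **Reporting:** give the severe related SAE proportion with an exact 95% interval, and state that no claim relative to surgery is drawn from it. Say whether the interval is one- or two-sided: with 1/13 the upper limit is 31.6% one-sided and 36.0% two-sided, on opposite sides of 34%.
- **Surgical comparison:** use the treatment-related complications of any grade already collected under the second primary outcome. Present them descriptively and by component beside the non-surgical figures in section 9.4.1 (9%, 3%, 4% and 3%; about 19% if they do not overlap). Do not test them against 34%. That figure contains operative events, while the trial's count would add radiotherapy effects such as tiredness, swallowing discomfort and cough (section 9.4.1). The last component is reduced sweating in section 9.4.1 but excess sweating in section 16.4.1, and this must be reconciled first.

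The cost is revised text and a more modest headline claim. No new data or patients are needed.
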